### Sample size

Sample size was calculated using resources available at the Laboratory of Epidemiology and Statistics (LEE) website of the Dante Pazzanese Institute (http://www.lee.dante.br/pesquisa/amostragem/qua_2_medias.html). The calculation was based on data provided by Sönmezer et al. [48]. In that article, Sönmezer et al. detected a significant difference in the serum levels of AMH in the first month after surgery, with a measurement of 2.72 ± 1.49 for the patients who received the hemostatic matrix versus 1.64 ± 0.93 for the patients who received bipolar coagulation. Here, we assume that the standard deviation in the AMH measurement of 1.49 in the first month was significant, since that was the number that generated the largest sample size when compared with other values from that article. The difference to be detected is 1.08, which corresponds to the mean difference in AMH in the first month between the patients who receive hemostatic matrix and those who receive bipolar coagulation. On those grounds, and for a statistical power of 80% (*p* = 0.05), each group would have to have 23 participants. Considering possible losses, the sample will be increased by 20% to 28 participants per group, making a total of 84 women. It should be noted that the present sample maybe not detect a powerful difference in treatment arms, but relevant contributions are expected.

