### Procedures for the assessment of ovarian reserve

Ovarian reserve will be assessed by measuring AMH and by performing AFC using ultrasonography at four different moments: before surgery and one, three, and six months after surgery. Serum samples will be obtained from each participant and centrifuged for 10 min to separate the cell contents and debris. Each serum sample will be transferred to polypropylene tubes and stored at − 80 °C.

AMH levels will be quantitatively measured using enzyme-linked immunosorbent assay (ELISA) (Diagnostic Systems Laboratories, Webster, TX, USA), with a detection sensitivity of 0.006 ng/mL.

Transvaginal ultrasonography for antral follicle count will be performed during the early proliferative stage (days 3–7 of the menstrual cycle) and the total number of follicles with diameters < 10 mm will be considered.

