#### Data processing and analysis

The data will be double-entered by two different data entry operators, using the Epi Info software program, version 7.2. The two databases will be compared using the Validate function of the Epi Info software program. Statistical analysis will be conducted using the Microsoft Excel software and the SPSS statistical software package for Windows, version 19.0.0. The data entry operators and the statistician will be blinded in that they will receive the data marked simply as A, B, or C and will be unaware of which procedure corresponds to which letter. A significance level of 5% will be determined for all the statistical tests.

To analyze the numerical variables AMH and AFC, the Kolmogorov–Smirnov test of normality will be used to determine the type of analysis to be performed. If distribution is normal, two-way analysis of variance (ANOVA) will be used, with the group representing an independent factor (bipolar energy × suture × hemostatic matrix). Another factor to be analyzed will be paired time points (before surgery × 1 month × 3 months × 6 months). If distribution is not normal, non-parametric tests will be used to analyze the variables.

The Kruskal–Wallis test will be used to compare variables between the three groups at each time point, with Tukey’s multiple comparison test being used when comparisons are statistically significant. The Friedman test will be used to perform intra-group comparisons at the four evaluation moments, with Tukey’s multiple comparison test being used when they are significant.

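### If AMH and AFC pass the normality test, the four-visit paired ANOVA in its standard form drops any woman who misses one visit, including her month-1 value, from the group comparison

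*Protocol article*

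**What the plan says.** Ovarian reserve is measured "at four different moments: before surgery and one, three, and six months after surgery" (Procedures for the assessment of ovarian reserve).

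Under Data processing and analysis, a normality test chooses between two routes.

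- **Normal:** "If distribution is normal, two-way analysis of variance (ANOVA) will be used, with the group representing an independent factor". The second factor is visit: "Another factor to be analyzed will be paired time points (before surgery × 1 month × 3 months × 6 months".
- **Not normal:** "The Kruskal–Wallis test will be used to compare variables between the three groups at each time point" and, separately, "The Friedman test will be used to perform intra-group comparisons at the four evaluation moments".

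The Sample size section rests on a between-group difference at month 1: "The difference to be detected is 1.08, which corresponds to the mean difference in AMH in the first month", with SD 1.49, 80% power and 23 women per group. It then allows for attrition: "Considering possible losses, the sample will be increased by 20% to 28 participants per group".

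The article does not say how a woman with a missed visit is handled.

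**The concern.** A classical ANOVA with a four-level paired factor and the Friedman test both work on complete rows. The protocol plans for losses, yet names two methods that cannot use a woman with a gap.

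In the normal route this reaches the comparison on which the trial was sized. A woman seen before surgery and at month 1, but not at month 3 or 6, is removed from the group comparison although her month-1 AMH was measured.

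Two things are at stake:

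- **Precision.** The Sample size section itself concedes that the trial may be short of power, so discarding measured values is hard to justify.
- **Bias.** Completers represent all randomized women only if staying is unrelated to ovarian reserve. Infertility is one of the listed indications for surgery (Eligibility criteria), so attendance that depends on ovarian recovery is plausible, though the document does not report it.

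**Working it through.** **1. What each named test needs**

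| Test | Route | Question | Woman with months 0 and 1 only |
|---|---|---|---|
| Group × paired-time ANOVA | normal | between and within groups | dropped entirely |
| Kruskal–Wallis at each visit | not normal | between groups | kept at months 0 and 1 |
| Friedman over four visits | not normal | within group | dropped entirely |

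A check on simulated data (28 women, 5 without the last visit) agreed. A standard repeated-measures ANOVA routine refused the unbalanced data, and the Friedman test gave no result until the incomplete women were removed.

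**2. The protocol's own figure**

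Inputs from Sample size: difference 1.08, SD 1.49, alpha 0.05, power 80%. Formula: n = 2[SD(z_alpha + z_power)/difference]².

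- One-sided: 2[1.49(1.645 + 0.842)/1.08]² = 23.5, close to the stated 23.
- Two-sided: 2[1.49(1.960 + 0.842)/1.08]² = 29.9, which does not match.
- Allowance: 23 × 1.2 = 27.6, rounded up to 28.

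The article does not state sidedness. That is a separate matter, so power is shown both ways below.

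**3. Women retained per arm, starting from 28**

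The article gives no miss rates by visit, so these are assumptions.

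- If 20% miss at least one visit: 28 × 0.8 = 22.4 complete.
- If each of the three follow-up visits is missed independently with probability p, 28(1 − p)³ are complete and 28(1 − p) have a month-1 value:

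| p | complete | with month-1 value |
|---|---|---|
| 5% | 24.0 | 26.6 |
| 7% | 22.5 | 26.0 |
| 10% | 20.4 | 25.2 |

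- If every loss comes before month 1, the two columns are equal.

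**4. Power at month 1**

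Two-sample t-test, difference 1.08, SD 1.49, n rounded. This stands in for the ANOVA contrast.

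| p | n complete / with month 1 | two-sided | one-sided |
|---|---|---|---|
| 5% | 24 / 27 | 69% / 74% | 80% / 83% (at 26.6) |
| 10% | 20 / 25 | 61% / 71% | 73% / 81% |

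For reference, all 28 per arm give 76% two-sided and 85% one-sided.

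**5. Possible bias**

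Assume that 20% of one arm leaves after month 1, with log-odds of leaving rising by 0.5 or 1.0 per SD lower month-1 AMH (odds ratio 1.6 or 2.7). The completer mean in that arm then rises by about 0.096 or 0.173 SD.

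- SD 1.49: 0.14 or 0.26 ng/mL, which is 13% or 24% of 1.08.
- SD 0.93 (the bipolar arm's value in Sample size): 0.09 or 0.16 ng/mL, which is 8% or 15% of 1.08.

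If the same mechanism acts in every arm, much of the shift cancels in the contrast.

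**The case against.** The strongest reply has four parts.

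- **The non-normal route is largely safe.** A reader might infer that both routes discard the month-1 values on which the trial was sized. The text does not support that. That contrast is between groups, and Kruskal–Wallis tests it visit by visit among all women measured. Friedman answers only the within-group question. This part stands in full. What remains in that route is that change over time, which bears on the Discussion's question of whether surgery itself harms the ovary, is assessed on completers only.
- **Complete-case use is inferred.** The article never says that women with a gap are excluded, and missing-data rules may stand in a document not shown. Their absence is no finding. The point rests on the named methods, which in their standard form need complete rows.
- **The 20% allowance may already cover this.** One might read it as set for month 1 alone, but the article ties it to no visit. Read as total loss through month 6, it leaves 22.4 completers against 23 required, so the plan roughly meets its own target. That stands, but it does not justify discarding values already measured.
- **The size is assumed.** Independent 10% misses leave 27% incomplete, which is more than the 20% allowed for. At 5% the two-sided loss is about 5 points. Part of the low two-sided power comes from the sample size itself, which gives only 76% with all 28.

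**Conclusion.** The concern holds for the normal route and, within groups only, for the Friedman test. It does not extend to the between-group comparison in the non-normal route.

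In the normal route the plan, followed in its standard form, loses between nothing (all dropout before month 1) and about 10 points of two-sided power (8 one-sided) at 10% independent misses per follow-up visit. Bias in the contrast is possible but conditional. It needs dropout that depends on recovery and differs by arm, and under the one-arm scenario above it is about 0.09 to 0.26 ng/mL.

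The documents supply neither a miss rate nor a dropout mechanism, so these figures show a range and are not forecasts. This is a cheap improvement worth making; it does not invalidate the trial.

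**What to change.** Replace the paired-time ANOVA, and Friedman for change over time within an arm, with one linear mixed model for repeated measures: arm, visit, arm × visit, unstructured covariance, fitted to all available values. Take the between-arm contrasts at each visit, including month 1, and the within-arm changes from that model.

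Handle skewness within the model by analysing log AMH and a suitably transformed or count-based AFC. Kruskal–Wallis at each visit and the completer analysis can stay as sensitivity analyses.

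The model uses a woman's observed values even if she later drops out, so it deals with dropout that depends on those values. It does not remove bias from dropout that depends on values never observed.

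Cost: analysis wording only, with no extra women or visits. The SPSS package already named has a mixed-model procedure. The downsides are a slightly more complex model and results on a transformed scale. Trial status reports 32 of 84 women randomized by 24 April 2019, so at that date the change could still be made before most of the data existed.

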### Data collection, processing, and analysis procedures

#### Data collection instrument

A specific form will be developed for the study. It will be in the form of a handwritten log. Prospective data collection will be performed on the day of the intervention and subsequently for the data following the intervention. The follow-up items for the participants are presented in Table 1 and Fig. 2.

**Table 1 Tab1:** The standard protocol items and timing of the measurements

Measurements	T0	T1	T2	T3
Age, BMI, complaints, gynecological and obstetric history	x			
The largest cyst diameter	x			
Side of pathology	x			
Surgery: duration, blood loss, perioperative complications, ASRM classification	x			
Hemoglobin	x			
Bipolar coagulation (number of points coagulated)	x			
Suture (number of stitches sutured)	x			
Hemostatic (number of hemostatic used)	x			
AMH	x	x	x	x
AFC in affected ovary	x	x	x	x
AFC in the contralateral ovary	x	x	x	x
Total AFC	x	x	x	x

*BMI* body mass index, *T0* before surgery, *T1* one month after surgery, *T2* three months after surgery, *T3* six months after surgery

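### Neither analysis branch names a between-arm comparison adjusted for pre-surgery AMH or AFC, which costs power and leaves the main tests exposed to chance baseline imbalance

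*Protocol article*

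**What the plan says.** All references are to the Protocol article.

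- **Baseline is available.** The section headed Procedures for the assessment of ovarian reserve gives the schedule: "Ovarian reserve will be assessed by measuring AMH and by performing AFC using ultrasonography at four different moments: before surgery and one, three, and six"; the last three are counted in months from the operation. Table 1 marks AMH and AFC at T0, T1, T2 and T3.
- **Normal branch.** Data processing and analysis: "two-way analysis of variance (ANOVA) will be used, with the group representing an independent factor". Then: "Another factor to be analyzed will be paired time points", with the pre-surgery value listed as the first of four levels. Baseline is therefore part of the outcome. No covariate is named, and the interaction is not mentioned.
- **Non-normal branch, between arms.** The Kruskal–Wallis "test will be used to compare variables between the three groups at each time point". As written, this includes T0.
- **Non-normal branch, over time.** "The Friedman test will be used to perform intra-group comparisons at the four evaluation moments".
- **Error level.** "A significance level of 5% will be determined for all the statistical tests". Sidedness is not stated.

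The article mentions no baseline covariate, no change-from-baseline outcome and no stratification of the randomization by ovarian reserve. Because the tests are fixed by name, this is a stated choice and not detail left to a later analysis plan.

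**The concern.** The first question in the Discussion is whether bipolar energy damages the ovary. That is a question about reserve after surgery given reserve before it, compared between arms. Pre-surgery AMH and AFC are likely to be strong predictors of the post-surgery values, and the plan collects them without using them in the treatment comparison.

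Two things are at stake.

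- **Power.** The Sample size section itself concedes that power may be limited. The Discussion says that if no significant difference is found, surgeons may choose by convenience. Avoidable loss of power makes that reading more likely to be wrong.
- **Chance imbalance.** With about 23 analysable women per arm, arms can differ in starting reserve by an amount that matters against the target difference. A comparison of raw post-operative values carries part of that difference into the treatment estimate.

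**Working it through.** **Inputs from the Sample size section:** difference 1.08 (month-1 AMH, matrix versus bipolar), SD 1.49, 80% power, p = 0.05, 23 per group, raised by 20% to 28.

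**Assumptions:** the correlation ρ between baseline and follow-up, which the article does not give (range 0.3 to 0.8 below); a baseline SD equal to 1.49; two-sided 5%.

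**1. The plan's own figure.** n per arm = 2 × [SD × (z_α + z_β) / difference]². One-sided 5% gives 23.5, so 24, close to the stated 23. Two-sided 5% gives 29.9, so 30. The sidedness question is separate. It matters here only because two-sided power at 23 per arm starts below 80%.

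**2. Power at one visit, 23 per arm.** Unadjusted: the standard error (SE) is 1.49 × √(2/23) = 0.439, the noncentrality is 1.08/0.439 = 2.46 and noncentral-t power is 67%. Baseline adjustment (ANCOVA) replaces the SD by 1.49 × √(1 − ρ²). A comparison of change scores replaces it by 1.49 × √(2(1 − ρ)).

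| ρ (assumed) | ANCOVA SD | ANCOVA power | Change-score SD | Change-score power |
|---|---|---|---|---|
| 0.3 | 1.421 | 71% | 1.763 | 53% |
| 0.5 | 1.290 | 79% | 1.490 | 67% |
| 0.6 | 1.192 | 85% | 1.333 | 77% |
| 0.7 | 1.064 | 92% | 1.154 | 87% |

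**3. Non-parametric branch by simulation** (2,000 runs, three arms of 23, normal data, equal correlation between visits, true arm effects 0/1.08/1.08). Month-1 Kruskal–Wallis power is about 66–69% whatever ρ is. Rank-based ANCOVA gives 68%, 79%, 91% and 98% at ρ = 0.3, 0.5, 0.7 and 0.8.

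**4. ANOVA branch.** Assume equal effects at T1–T3 and compound symmetry. In units of SD²:

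- ANCOVA on the post-operative mean has variance (1 + 2ρ)/3 − ρ², which is 0.417 at ρ = 0.5 and 0.310 at ρ = 0.7.
- The change contrast (post-operative mean minus T0) has variance (1 + 2ρ)/3 + 1 − 2ρ, which is 0.667 and 0.400. Its efficiency relative to ANCOVA is 0.417/0.667 = 62.5% and 0.310/0.400 = 77.5%.
- The group main effect over all four levels carries only 0.75 of the effect, with variance (1 + 3ρ)/4. Its relative efficiency is 0.75² / [(1 + 3ρ)/4] × the ANCOVA variance: 37.5% at ρ = 0.5 and 22.5% at ρ = 0.7.

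In the same simulation the interaction has 54%, 72%, 93% and 100% power at ρ = 0.3, 0.5, 0.7 and 0.8. The main effect has 77%, 64%, 55% and 53%. ANCOVA on the post-operative mean has 96%, 96%, 99.5% and 100%.

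**5. Chance imbalance.** The SE of a baseline AMH difference between two arms of 23 is 0.44, so its 95% range is ±1.96 × 0.44 = ±0.86, against a target of 1.08. An imbalance of size b shifts the unadjusted post-operative difference by ρ × b. With b = 0.44 that is 0.22 at ρ = 0.5 and 0.31 at ρ = 0.7. In simulation under no effect (ρ = 0.5 to 0.8), Kruskal–Wallis rejects in 4–5% of all trials. It rejects in 8–10% of trials where the baseline arm means span more than 0.54, and in 13–22% of those where they span more than 0.88. The wider span occurred in about 10–11% of simulated trials.

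**The case against.** **The ANOVA does handle baseline.** Group crossed with four paired time points ordinarily yields a group × time interaction, which compares change between arms and removes a chance baseline difference. This stands. A reader might infer that both branches leave imbalance uncorrected, or that the ANOVA has only 22.5–37.5% of attainable efficiency. The documents do not support either: those figures describe the group main effect alone. What remains is that the article does not say which term is the treatment test, and that a change comparison is less efficient than ANCOVA.

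**Kruskal–Wallis after surgery is a direct randomized comparison.** This also stands, and it matches the sample-size target, a month-1 difference. A reader might infer that the non-parametric branch leaves only significance in one arm set against non-significance in another. It does not, since between-arm tests at one, three and six months are planned. The Friedman tests also bear on the Discussion's second question, whether surgery itself does the damage. The narrower point holds: no between-arm test in that branch uses the starting value.

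**The tests are valid.** Correct. Averaged over randomizations, type I error is about 5%, so a claim of invalid inference would be wrong.

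**The gain depends on an unknown correlation.** Correct. At ρ = 0.3 the gain is only 67% to 71%. The Background says that the post-operative fall tends to recover, so the correlation may differ by visit. Nor do the documents support a claim that the plan has barely 40% power. That would need a treatment ratio such as 1.35, which appears nowhere in them. The means in the Sample size section give 2.72/1.64 = 1.66.

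**Conclusion.** The point holds as an improvement in efficiency and in protection against imbalance that costs nothing in data. It is not an error that invalidates the trial. Neither branch names a baseline-adjusted between-arm comparison. The non-parametric branch has none that uses baseline in any form, and the ANOVA branch has one only through an interaction that the article does not designate.

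At one visit with 23 per arm, adjustment adds about 4 percentage points of power at ρ = 0.3, 12 at 0.5, 18 at 0.6 and 25 at 0.7. These gains rest on the plan's difference and SD, two-sided 5%, approximate normality and an assumed ρ. The imbalance figures also assume that the baseline SD equals the month-1 SD of 1.49. The ANOVA efficiencies further assume equal effects at all three post-operative visits and compound symmetry.

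**What to change.** In Data processing and analysis, make the between-arm comparison at T1, T2 and T3 baseline-adjusted for both AMH and AFC. Use either ANCOVA at each visit, or a mixed model with arm, visit, arm × visit and the baseline value as covariate, on a log or rank scale if the data are skewed. Report adjusted pairwise differences, or ratios on the log scale, with 95% confidence intervals. Drop the between-arm test at T0. Keep within-arm change over time as supplementary description.

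If the two-branch structure is kept, the least that is needed is to name the group × time contrast as the treatment test in the ANOVA and to add a between-arm comparison of change, or preferably a rank-based ANCOVA, to the non-parametric branch.

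Age as a covariate, a count model for AFC and the handling of missed visits are optional extras that this point does not depend on.

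The cost is a change of wording and a standard model in the named software. T0 AMH and AFC are already in Table 1. The Trial status section reports 32 of 84 women randomized by 24 April 2019. The change should be dated and made before the group codes are linked to outcomes.

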### Eligibility criteria

Women aged at least 18 years, with regular menstrual cycles (21–35 days) and a diagnosis of a unilateral ovarian cyst suggestive of an endometrioma, with an indication for laparoscopic surgery to remove the cyst due to pelvic pain, infertility, or persistence of the cyst will be eligible for the study. Exclusion criteria are: previous ovarian surgery; endocrine dysfunction (diabetes, thyroid disorders, hyperprolactinemia, adrenal disease, polycystic ovary syndrome); use of hormones in the past three months; suspected malignant ovarian tumor requiring oophorectomy; history of chemotherapy or radiotherapy; coagulation disorders; pregnancy; and autoimmune disease.

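### If AMH or AFC is judged non-normal, the only between-arm test is Kruskal–Wallis on raw values at each visit. It is valid but ignores each woman's measured preoperative value, so precision is lost.

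*Protocol article*

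**What the plan says.** The section on data processing and analysis sends AMH and AFC down one of two routes after a Kolmogorov–Smirnov test. If normality holds, a two-way ANOVA is used with group as one factor; the second factor is described as "Another factor to be analyzed will be paired time points (before surgery × 1 month × 3 months × 6 months". The preoperative visit is therefore a level of the time factor in that branch.

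Otherwise, "If distribution is not normal, non-parametric tests will be used to analyze the variables". For the comparison between arms, a Kruskal–Wallis test "will be used to compare variables between the three groups at each time point", with Tukey comparisons after a significant result. For change over time: "The Friedman test will be used to perform intra-group comparisons at the four evaluation moments". The Friedman test uses the preoperative value, but only inside each arm.

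The preoperative values exist. The section on assessment of ovarian reserve has AMH and AFC measured "at four different moments: before surgery and one, three, and six months after surgery". Table 1 records "Age, BMI, complaints, gynecological and obstetric history" at T0. The randomization section describes a numbered list of 84 and mentions no stratification.

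**The concern.** The trial asks whether the hemostatic method damages the ovary, that is, whether a woman loses reserve relative to where she started. In the rank branch no change score, baseline covariate or other link to the preoperative value enters the between-arm test. The same test is also run at the preoperative visit, where any difference between randomized arms is chance.

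With 23 to 28 women per arm, two things follow. Variation between women that their own preoperative value could explain stays in the error term, so a real effect is missed more often than necessary. In addition, part of any chance difference in starting reserve is carried into the estimate.

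A missed effect has consequences here. The sample size section concedes that power may be limited, and the Discussion says that if no significant differences are found, surgeons may choose by convenience and availability.

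**Working it through.** **Inputs from the sample size section.** Month-1 AMH is 2.72 ± 1.49 (hemostatic matrix) and 1.64 ± 0.93 (bipolar). The target difference is 2.72 − 1.64 = 1.08, the planning SD 1.49, power 80%, p = 0.05, with 23 per group raised to 28.

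**Assumed, because the documents do not give them.** The pre/post correlation r, taken as 0.3, 0.5, 0.7 and 0.8. The preoperative SD, taken as 1.49, as 0.93, or as the pooled value √[(1.49² + 0.93²)/2] = 1.24. All three derive from month-1 postoperative SDs.

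**Plan's own figure.** n = 2[(z_α + z_0.80) × SD / 1.08]².
- SD 1.49: one-sided 23.5, so 24; two-sided 29.9, so 30.
- SD 1.24: two-sided 20.8, so 21.

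The stated 23 is close to the one-sided figure with SD 1.49 and to the two-sided figure with the pooled SD. The text does not state sidedness, so both SDs are carried forward below.

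**Effect of adjustment on power.** Adjusting for the preoperative value reduces the residual SD to SD × √(1 − r²). With SD 1.49 this is 1.42, 1.29, 1.06 and 0.89 at the four values of r. Two-sided noncentral-t power for 1.08, one pair of arms (the one degree of freedom spent on the covariate is ignored):

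| SD | n per arm | Unadjusted | r = 0.3 | r = 0.5 | r = 0.7 | r = 0.8 |
|---|---|---|---|---|---|---|
| 1.49 | 23 | 67% | 71% | 79% | 92% | 98% |
| 1.49 | 28 | 76% | 80% | 87% | 96% | 99% |
| 1.24 | 23 | 82% | 86% | 92% | 98% | >99% |
| 1.24 | 28 | 89% | 92% | 96% | 99% | >99% |

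**Check on the rank tests themselves.** These are t-test figures, so the three-arm comparison was also simulated (23 per arm, 3,000 runs, normal scores, one arm lower by 1.08/1.49 SD). Kruskal–Wallis had 66–69% power at every r. Rank ANCOVA on the preoperative value had 71%, 79%, 92% and 97% at r = 0.3, 0.5, 0.7 and 0.8. With no effect, Kruskal–Wallis rejected in 4.4–5.0% of runs.

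**Chance preoperative gap.** The SE of the difference between two arms of 28 is SD × √(2/28), which is 0.40, 0.33 and 0.25 for SD 1.49, 1.24 and 0.93. The probability of a gap of 0.5 or more in either direction is 21%, 13% and 4%. Only r times the gap carries forward: a gap of 0.5 shifts the unadjusted difference by 0.15, 0.25, 0.35 or 0.40 at the four values of r. Against the target of 1.08 that is 14% to 37%.

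**The case against.** - **No validity error.** Kruskal–Wallis holds its level under randomization, and its null distribution already allows for chance imbalance. This stands. A reader might infer that the planned test is biased or gives false positives; neither the documents nor the simulation supports that.
- **The gain rests on an unknown r and a chosen SD.** This stands. At r = 0.3 the gain is about 4 points. With the pooled SD, unadjusted power is already 82% at 23 per arm and 89% at 28. It limits the size that can be claimed, but adjustment gains power at every r shown.
- **Preoperative spread.** Because the criteria admit "Women aged at least 18 years, with regular menstrual cycles" with no stated upper age limit, a reader might infer that most of the postoperative spread predates surgery. That needs r² above 0.5, so r above 0.71, and no r is given. The other criteria (regular cycles, no endocrine dysfunction, no previous ovarian surgery, no recent hormones) also narrow the population.
- **Age.** A benefit from age beyond the preoperative value is plausible but cannot be quantified from the documents, and the two would overlap.
- **Only one branch is affected.** Correct. In the normal branch the group-by-time term can use the preoperative visit. The rank branch is still a realistic outcome: the month-1 SDs are 55% (1.49/2.72) and 57% (0.93/1.64) of their means, a pattern seen in right-skewed data. If AMH were log-normal with log SD 0.52 (an assumption), simulation has a Lilliefors-type Kolmogorov–Smirnov test rejecting in about 39% of samples of 23 and 89% of samples of 84.
- **Detail for a SAP.** Covariate lists are often left there. Here, however, the article names the between-arm test itself, so the choice is already made.

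**Conclusion.** The point holds as a matter of efficiency in the non-normal branch. The named between-arm test is valid on average over randomizations, but it discards a measurement taken on the same outcome before surgery.

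The cost at 23 per arm, two-sided, ranges from about 4 points of power (r = 0.3, either SD) to about 31 points (r = 0.8, SD 1.49: 67% against 98%). At r = 0.5 it is 12 points with SD 1.49 and about 9 with SD 1.24. The chance of a preoperative gap of at least 0.5 between two arms of 28 is 4% to 21% depending on the SD, and only the fraction r of such a gap reaches the result. All of these sizes depend on assumed values of r and of the preoperative SD. The change is worth making but does not decide whether the trial is sound.

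**What to change.** In the section on data processing and analysis, replace the per-visit Kruskal–Wallis test as the between-arm analysis with one pre-specified baseline-adjusted analysis of the postoperative values:

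- **AMH:** ANCOVA of log AMH on arm and preoperative log AMH, with a stated rule for values below the assay limit of 0.006 ng/mL.
- **AFC:** rank ANCOVA, comparing arms on postoperative AFC adjusted for preoperative AFC.
- **Age:** an optional covariate, to be named in advance if used.
- **Preoperative visit:** describe the arms and do not test them against each other.

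The Friedman test may stay as a within-arm description. No patient, visit or measurement is added, since the preoperative values and age are already in Table 1. The article reports 32 of 84 women randomized and a statistician who sees only the letters A, B and C, so the wording can be fixed before the labels are unblinded.
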